**Methods/design:**

This is a randomized, single-blind, two-arm, controlled trial in patients with rheumatoid arthritis visiting outpatient rheumatology clinics in Karachi, Pakistan. We will enroll patients with established diagnosis of rheumatoid arthritis over 3 months. The patients would be randomized through a computer-generated list into the control group, i.e., usual care or into the intervention group, i.e., pharmaceutical care, in a ratio of 1:1, after providing signed written consent. The study will take place in two patient-visits over the course of 3 months. Patients in the intervention group would receive intervention from the pharmacist while those in the control group will receive usual care. Primary outcomes include change in mean score from baseline (week 0) and at follow up (week 12) in disease knowledge, adherence to medications and rehabilitation/physical therapy. The secondary outcomes include change in the mean direct cost of treatment, HRQoL and patient satisfaction with pharmacist counselling.

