### Objectives

The primary objective of the study is to evaluate the effectiveness of a multifactorial educational intervention on patient knowledge of RA and adherence to treatment. This intervention would be provided by a pharmacist. The secondary objectives are to assess the impact of the intervention on the cost of treatment, quality of life and patient satisfaction.

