### Study plan

The process will start after patients attend the study explanation session and consent to participate. The patients who refuse to participate will be provided regular hospital care. Patients who consent to participate will sign the patient consent form and will be screened for eligibility. Ineligible patients will be excluded from the study and given regular hospital care. Eligible patients will be randomized by computer software into the IG or CG. Patients’ baseline data will be recorded. Enrolled patients’ demographic data will be documented at baseline. Patients will have their anthropometric measurements, i.e., weight, height, etc. noted in addition to their socio-demographic data. Moreover, the patients will be assessed for the outcome measures. The patients randomized into the IG will be provided pharmacist intervention. At the follow-up appointment, i.e., after 3 months (week 12) from baseline (week 0), the same data will be recorded from patients in both treatment groups.

Attention is paid to achieving high patient-retention rates by comprehensively briefing the patients and answering their queries. In the case of loss to follow up, the rheumatologist and the hospital’s front desk staff will establish contact with the patient, try to convince them to participate and if not, document the reason for leaving the study. The whole study will encompass two visits in due course (Fig. 1).

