### Statistical analysis

The statistical analysis will be conducted by a statistician who will be blinded to patient-group allocation. The analysis will be carried out using SPSS version 22 (IBM SPSS, Armonk, NY, USA). The analysis will consist of a per-protocol set that includes participants who have completed the study as per the defined protocol. The significance level will be set at 5% and a two-tailed test will be used. Continuous data will be descriptively analysed using the Mann-Whitney U test, while the chi-square test will be used to analyze categorical variables by comparing them in the two groups at the same time point. Confirmatory analysis will be carried out using the Wilcoxon signed-rank test to analyze differences in the mean values for disease knowledge, adherence to treatment and medications and the cost of treatment after 3 months, i.e., baseline within-subject analysis. Multinomial logistic regression will be used to interpret the odds ratios for the secondary outcome, i.e., patient satisfaction with pharmacist counselling. There will be no interim data analysis.

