Outcome selection is an important area in designing clinical trials. The selected outcome must be relevant to patients, health care professionals and policy makers. Appropriate outcomes help in evaluating, disseminating and generalizing the findings of a trial [34]. There is a plethora of studies that evaluate disease knowledge, medication adherence and quality of life as prime treatment outcomes for chronic illnesses [4, 11, 32, 33]. However, treatment in RA may include rehabilitation/physical therapy to minimize mobility-related problems as a consequence of disease. It is worthwhile mentioning that rehabilitation/physical therapy was reported as an outcome by Kirkham and colleagues in their observational review of randomized trials over the last 50 years [34]. Therefore, adherence to rehabilitation/physical therapy is considered as another treatment outcome in our study. Thus, the primary outcomes are change in mean scores for disease knowledge, medication adherence and rehabilitation/physical therapy adherence. Since RA mostly affects middle-aged individuals, studies report that this age group is mostly affected with respect to productivity, which may add to the financial burden on the patient. Therefore, a change in the mean direct cost of treatment and patients’ HRQoL were considered as secondary outcomes.

One of the most important elements to assess in studies that evaluate the impact of counselling on treatment outcomes is the quality of counselling. Patient satisfaction could be considered as an indirect indicator of quality of service. Not only is it important from a subjective point of view, but this satisfaction could translate into future visits, trust and recommendation to others, thereby increasing the likelihood of pharmaceutical care delivery among the masses. Saleem and colleagues mentioned the absence of this indicator as a limitation in their study [11]. Therefore, patient satisfaction with pharmacist counselling is designated as another secondary outcome.

As of now, there have been no trials conducted in Pakistan that evaluate the effectiveness of a multi-dimensional pharmacist intervention in improving treatment outcomes in patients with RA. The results of this trial could set the foundation for future delivery of care for such patients in Pakistan and in other parts of the globe.

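### HRQoL, presented as a change-type secondary outcome with baseline data collected, is left to a general unadjusted Mann-Whitney rule that makes no use of baseline EQ-5D-5L as a covariate

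*Protocol article*

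**What the plan says.** **The outcome.** The Abstract (Methods/design) states: "The secondary outcomes include change in the mean direct cost of treatment, HRQoL and patient satisfaction with pharmacist counselling". The Discussion says that "a change in the mean direct cost of treatment and patients’ HRQoL were considered as secondary outcomes". The Objectives section makes the effect on quality of life an explicit aim: "The secondary objectives are to assess the impact of the intervention on the cost of treatment, quality of life and patient satisfaction".

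**Data collection.** The Study plan describes the baseline visit thus: "Moreover, the patients will be assessed for the outcome measures". At week 12, "the same data will be recorded from patients in both treatment groups". EQ-5D-5L should therefore be available at both visits.

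**The analysis.** The Statistical analysis section has three layers:
- A general rule: Mann-Whitney for continuous data, described as descriptive, and chi-square for categorical variables, the latter by "comparing them in the two groups at the same time point".
- A confirmatory within-subject Wilcoxon signed-rank analysis of "differences in the mean values for disease knowledge, adherence to treatment and medications and the cost of treatment after 3 months".
- A multinomial logistic regression for patient satisfaction.

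Neither HRQoL nor EQ-5D-5L is mentioned there. The mixed model in the Intervention section concerns implementation across pharmacists, not outcomes.

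**The concern.** Of the three secondary outcomes, cost is assigned to the Wilcoxon analysis and satisfaction to a regression. HRQoL alone has no analysis assigned by name, so only the general rule can cover it. That rule yields a rank test with no covariates and descriptive status, for an outcome that the Objectives section ties to the effect of the intervention.

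Two things are at stake. First, the analysis fits the endpoint loosely: the endpoint reads as a change, and no analysis of change in HRQoL is specified. Second, the baseline EQ-5D-5L score is collected in both arms, yet no covariate adjustment uses it. Baseline value is commonly the best single predictor of a quality-of-life score three months later, so leaving it out gives away precision that has already been paid for.

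**Working it through.** **Inputs from the article**
- Total sample 619 and drop-out 20% (Sample size).
- Allocation 1:1 (Design and setting).
- Two-sided 5% level (Statistical analysis).
- 80% power (Sample size), used for the detectable differences.

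The article gives no power figure for HRQoL, so there is none to reproduce. The 619 was derived for adherence. It does not follow from its own stated inputs (16% versus 9% gives 350 per arm, 700 in total, 875 after 20% drop-out), but that is a separate matter. Here 619 serves only as the planned enrolment.

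**Assumptions**
- A true HRQoL difference of 0.2 SD, for illustration.
- Baseline-to-week-12 correlation ρ of 0.3, 0.5 or 0.7.
- Equal SDs at the two visits.
- Approximate normality, including the Mann-Whitney relative efficiency of 0.955, which holds for normal data.

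**Completers per arm**
619 × 0.8 / 2 = 247.6.

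**Formulas**
Let f be the variance of the analysed quantity relative to a week-12 score:
- week-12 level: f = 1
- change score: f = 2(1 − ρ)
- baseline-adjusted: f = 1 − ρ²

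Power = Φ(0.2 × √(247.6 / (2f)) − 1.960). Detectable difference at 80% power = (1.960 + 0.842) × √(2f / 247.6).

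**Week-12 level, unadjusted**
- Power, comparison of means: 0.2 × √123.8 = 2.225; 2.225 − 1.960 = 0.265; Φ = 60.5%.
- Power, Mann-Whitney: 2.225 × √0.955 = 2.175; 2.175 − 1.960 = 0.215; Φ = 58.5%.
- Detectable difference: 2.802 × √(2/247.6) = 0.252 SD, or 0.252/√0.955 = 0.258 SD for Mann-Whitney.

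**By correlation (comparison-of-means basis)**

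| ρ (assumed) | f, change | Power, change | f, adjusted | Power, adjusted | Detectable, adjusted |
|---|---|---|---|---|---|
| 0.3 | 1.40 | 46.8% | 0.91 | 64.5% | 0.240 SD |
| 0.5 | 1.00 | 60.5% | 0.75 | 72.9% | 0.218 SD |
| 0.7 | 0.60 | 81.9% | 0.51 | 87.6% | 0.180 SD |

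The adjusted comparison is at least as precise as both alternatives at every ρ shown. A raw change score is less precise than the week-12 level when ρ is below 0.5 and more precise when ρ is above 0.5.

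**Would adding HRQoL to the Wilcoxon list do?** No. That test compares week 12 with week 0 within subjects. It does not compare the arms, so it cannot isolate the effect of the intervention.

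**The case against.** The strongest reply is that this is a condensed article, and the model for one secondary outcome may sit in a full protocol or analysis plan that is not shown. That defence stands for the choice between the EQ-5D-5L value and the VAS: a reader might count the silence on this as an error, but such detail is commonly left to the fuller documents. It carries less weight for the analysis rule, because the article fixes a rule for continuous data and an explicit list of confirmatory outcomes that leaves HRQoL out.

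A second reply is that change is not an unambiguous definition. In the Abstract the word would also have to cover satisfaction, which the Patient satisfaction section makes a week-12 proportion in the intervention arm only. The Discussion sentence can be parsed as a change in cost, plus HRQoL. The HRQoL outcome section mentions neither change nor time point. This is fair: change is the natural reading, not a certain one.

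A third reply concerns a stronger claim that a reader might infer: that HRQoL's only test is a comparison of levels at one time point, so that the trial cannot report a change in HRQoL. The text does not support this. The time-point phrase may attach only to the chi-square clause, so a Mann-Whitney test on change scores is neither stated nor excluded, and change can be computed from data recorded at both visits.

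Finally, no other outcome is baseline-adjusted either, and the gain depends on an unknown correlation. Both are true. At ρ = 0.3 the gain over the week-12 level is 4 percentage points (64.5% against 60.5%). The 0.955 factor also assumes normality; with skewed scores the rank test may lose nothing, or even gain, relative to a comparison of means.

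**Conclusion.** The point holds in a limited form. As written, HRQoL falls to an unadjusted Mann-Whitney test with descriptive status, which makes no use of baseline EQ-5D-5L as a covariate and matches a change-type endpoint poorly.

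A reader might infer bias; that does not follow. Under randomisation, a between-arm test of week-12 levels or of change scores is valid. The restriction to completers applies to all of these analyses alike. The loss is precision, and agreement between endpoint and analysis.

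For a 0.2 SD difference, the gain over 58–60% power on week-12 levels runs from small at ρ = 0.3 to substantial at ρ = 0.7. Against a change-score test the gain is largest at low ρ and shrinks to about 6 points at ρ = 0.7 (87.6% against 81.9%). These sizes rest on the assumed correlations, on 20% drop-out from 619 and on approximate normality. The omission itself rests on the text alone. This is a worthwhile improvement to a secondary analysis, not a threat to the trial.

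**What to change.** In the Statistical analysis section, name HRQoL and specify a between-arm comparison: regress the week-12 EQ-5D-5L score on arm and baseline EQ-5D-5L score, and report the adjusted mean difference with a 95% CI. With baseline in the model, the arm coefficient is the same whether the response is the week-12 score or the change, so this also serves the change reading of the endpoint.

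Because the score is bounded and may be skewed, use robust or bootstrap standard errors, or keep the Mann-Whitney test as a sensitivity analysis.

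The cost is a sentence or two and one extra model on data already collected. The price is reliance on a mean-based model for a bounded score, which the standard errors or the sensitivity analysis address. The Trial status section says that results are already being analysed. The choice should therefore be documented while the statistician is still blinded to allocation; if that is no longer possible, report it as post hoc.

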### Data monitoring

Data will be monitored in this study by independent health officials from the hospitals as designated by the ethical committee. The officials will monitor patient enrollment, study explanation sessions, patient consent documents, compliance to the defined protocol, data documentation and overall trial progress. A member of the ethical committee will serve as a protocol officer and will supervise those health officials. The protocol officer will serve as a communication link between the ethical committee and, health officials and investigators. The protocol officer, health officials and principle investigator constitute a steering committee that oversees the trial progress. In addition, the ethical committee will be updated by the steering committee on the progress of the study every 3 months.

### Data dissemination

The data forms collected from patients, would be handed over after statistical analysis, to the designated health officials from hospital staff who act as independent observers, and supervised by a designated member of the ethical review committee. The data forms will become property of the ethics committee and it will be at their discretion to decide if they wish to communicate the individual data with the rheumatologist and patients to appraise them about their treatment progress. This may prove helpful for patients and rheumatologists to analyze treatment progress and set future goals. Moreover, the results of the study will be communicated to the public in the form of publications. Authorship on publications would be decided as per the recommendations given by International Committee of Medical Journal Editors (ICMJE) [30]. The dataset obtained as a result of this study will be available solely for academic purposes on suitable request, subject to final approval from the ethics committee. The full study protocol is available at www.clinicaltrials.gov.

## Discussion

This study is designed as a randomized controlled trial that involves patients with RA. The nature of the disease demands self-care and home-based management; failure to understand or manage disease-aggravating symptoms lead to pain, mobility issues and increased suffering. This results in reduced productivity and quality of life [16, 31]. Therefore, it is important to derive ways to provide a patient-centric intervention that addresses these problems. These issues could be resolved through pharmaceutical care [12].

During the literature evaluation we came across the work of Abughosh and colleagues in which they evaluated the impact of telephone intervention by the pharmacist on medication adherence among patients with comorbid hypertension and diabetes mellitus [32]. The importance of patient-centered disease-education leaflets in increasing long-term patient knowledge has been demonstrated in a study [1]. Furthermore, in two randomized trials conducted in Pakistan, pharmaceutical care in the form of patient counselling significantly improved treatment outcomes in patients with hypertension. The outcomes included disease knowledge, medication adherence, HRQoL and blood pressure control [11, 33]. In this context, Lagger and colleagues reviewed 35 meta-analyses on the effectiveness of patient education, and concluded that patient education improves outcomes; however, the greatest benefits are seen when it is multi-dimensional and multi-disciplinary [2].

Therefore, we opted for a multi-dimensional intervention that could effectively address treatment outcomes in patients suffering from this disease. The composition of the intervention is based on previous research that has incorporated either of these aforementioned actions and evaluated their impact on improving patient-reported outcomes. The pharmaceutical care provided by a pharmacist in our study is multi-dimensional and encompasses patient counselling as well as disease education literature.

Outcome selection is an important area in designing clinical trials. The selected outcome must be relevant to patients, health care professionals and policy makers. Appropriate outcomes help in evaluating, disseminating and generalizing the findings of a trial [34]. There is a plethora of studies that evaluate disease knowledge, medication adherence and quality of life as prime treatment outcomes for chronic illnesses [4, 11, 32, 33]. However, treatment in RA may include rehabilitation/physical therapy to minimize mobility-related problems as a consequence of disease. It is worthwhile mentioning that rehabilitation/physical therapy was reported as an outcome by Kirkham and colleagues in their observational review of randomized trials over the last 50 years [34]. Therefore, adherence to rehabilitation/physical therapy is considered as another treatment outcome in our study. Thus, the primary outcomes are change in mean scores for disease knowledge, medication adherence and rehabilitation/physical therapy adherence. Since RA mostly affects middle-aged individuals, studies report that this age group is mostly affected with respect to productivity, which may add to the financial burden on the patient. Therefore, a change in the mean direct cost of treatment and patients’ HRQoL were considered as secondary outcomes.

One of the most important elements to assess in studies that evaluate the impact of counselling on treatment outcomes is the quality of counselling. Patient satisfaction could be considered as an indirect indicator of quality of service. Not only is it important from a subjective point of view, but this satisfaction could translate into future visits, trust and recommendation to others, thereby increasing the likelihood of pharmaceutical care delivery among the masses. Saleem and colleagues mentioned the absence of this indicator as a limitation in their study [11]. Therefore, patient satisfaction with pharmacist counselling is designated as another secondary outcome.

As of now, there have been no trials conducted in Pakistan that evaluate the effectiveness of a multi-dimensional pharmacist intervention in improving treatment outcomes in patients with RA. The results of this trial could set the foundation for future delivery of care for such patients in Pakistan and in other parts of the globe.

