### Outcomes

#### Primary outcome measurements

##### Treatment adherence

There are two modes of assessing treatment adherence, i.e., medication adherence and rehabilitation/physical therapy adherence. Both modes will be assessed after 3 months (week 12) from baseline (week 0). The Urdu version of the General Medication Adherence Scale (GMAS) [1] will be used for the assessment of adherence to medication and pharmacotherapy. The scale consists of eleven items that measure a patient’s adherence to medication and provide a score that could be interpreted as high, good, partial, low or poor adherence. There are four possible choices for each item, i.e., always, mostly, sometimes or never, which give a score of 0, 1, 2 or 3, respectively [22]. Adherence to rehabilitation/physical therapy will be assessed by utilizing the Urdu version of the General Rehabilitation Adherence Scale (GRAS). The scale consists of eight items that measure a patient’s adherence to physical therapy and provide a score that could be interpreted as high, good, partial, low or poor adherence. There are four possible choices for each item, i.e., always, mostly, sometimes or never, which give a score of 0, 1, 2 or 3, respectively ([name]: Development and validation of General Rehabilitation Adherence Scale (GRAS) in patients undergoing physical therapy for various musculoskeletal diseases. (unpublished work).

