### Sample size

Few randomized controlled trials have evaluated the effect of pharmacists’ educational interventions on adherence and disease knowledge among patients with RA. We reviewed several studies that could serve as a reference for calculation of sample size based on treatment effect. A study conducted by Clifford and colleagues assessed the effect of pharmacist educational advice on improving adherence [7]. Another study by Stockl and colleagues was nonrandomized and was limited to evaluating the effects of a telephone intervention by either a pharmacist or a nurse, on patients’ adherence to injectable RA medicines [8]. Azzopardi and colleagues used a different outcome measure to ours and included patients with RA prescribed methotrexate only [28]. Similarly, in another RCT, Petkova measured a different outcome [3].

We considered a study by Clifford and colleagues as a standard and calculated our sample size based on the primary outcome, i.e., adherence [7, 29]. It was taken as a reduction in self-reported nonadherence from 16% to 9% considering a (two-side) alpha value of 0.05 and statistical power of 80%, i.e., beta = 0.2. Considering a drop-out rate of 20%, we would require a total of 619 patients to successfully demonstrate a positive and statistically significant effect.

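### Three primary outcomes share one 5% level with no testing rule, while the trial is sized at the full 5% on a single adherence outcome whose scale is not named

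*Protocol article*

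**What the plan says.** The Abstract and the Discussion agree on three primary outcomes. The Discussion puts it as "Thus, the primary outcomes are change in mean scores for disease knowledge, medication adherence and rehabilitation/physical therapy adherence". The primary outcome section gives each its own instrument: RAKAS for knowledge, GMAS for medication adherence and GRAS for rehabilitation adherence. It is explicit that adherence is measured twice: "There are two modes of assessing treatment adherence, i.e., medication adherence and rehabilitation/physical therapy adherence".

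The Statistical analysis section sets one level: "The significance level will be set at 5% and a two-tailed test will be used". It then describes as confirmatory the tests of "differences in the mean values for disease knowledge, adherence to treatment and medications and the cost of treatment after 3 months". Knowledge and adherence stand side by side there, together with cost, which is elsewhere a secondary outcome. The section does not rank these tests or divide the 5% among them, and does not say how many must succeed.

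The Sample size section speaks of one primary outcome. The authors "calculated our sample size based on the primary outcome, i.e., adherence", using a fall in self-reported nonadherence from 16% to 9%, a two-sided alpha of 0.05 and 80% power. No scale is named.

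**The concern.** The sizing allots the whole 5% to a single adherence outcome. The analysis applies a 5% level to a set in which three outcomes carry the primary label. A reader cannot tell from the article which result makes the trial positive. If any one of the three may do so, the error rate of the headline claim is above 5%. If only adherence may do so, it is unclear whether GMAS or GRAS decides.

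The article says that the results could set the foundation for future care of these patients in Pakistan. What supports a positive conclusion should therefore be settled before the results are known.

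**Working it through.** **The plan's own figure.** The article states no family-wise error rate, so there is none to reproduce. The nearest related figure is the total of 619. With p1 = 0.16, p2 = 0.09, mean 0.125, two-sided alpha 0.05 and 80% power:

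n per arm = [1.960 × √(2 × 0.125 × 0.875) + 0.842 × √(0.16 × 0.84 + 0.09 × 0.91)]² / 0.07² = 350 after rounding up.

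That is 700 evaluable, and 700 / 0.8 = 875 with 20% drop-out. The figure of 619 is not reproduced. That is a separate matter and does not enter the error calculation. What matters here is that the sizing uses alpha 0.05 in full for one outcome.

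**Inputs for the error rate.**
- Number of primary outcomes: 3 (Abstract, primary outcome section, Discussion).
- Level: 5% two-sided (Statistical analysis).
- No interim analysis (Statistical analysis), so no alpha is used elsewhere.
- Correlation between outcomes: not given. Assumed equal for all pairs and varied from 0 to 0.9.
- Assumptions: all three nulls are true, each test is valid at 5%, and success on any one outcome counts as a positive trial.

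**Independent outcomes.** 1 − (1 − 0.05)³ = 1 − 0.8574 = 0.1426.

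**Correlated outcomes.** For three normal test statistics with common correlation ρ and c = 1.960:

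error = 1 − ∫ [Φ((c − √ρ·x)/√(1 − ρ)) − Φ((−c − √ρ·x)/√(1 − ρ))]³ φ(x) dx

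| Correlation | At least one false claim | Multiple of 5% |
|---|---|---|
| 0 | 14.3% | 2.9 |
| 0.2 | 14.0% | 2.8 |
| 0.5 | 12.5% | 2.5 |
| 0.7 | 10.9% | 2.2 |
| 0.9 | 8.4% | 1.7 |

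Cost is left out because the article labels it secondary. If it were counted because it is listed among the confirmatory tests, the independent figure would be 1 − 0.95⁴ = 18.5%.

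**Check that the remedies control the error.** Holm compares the smallest p-value with 0.05/3 = 0.0167, the next with 0.05/2 = 0.025 and the last with 0.05. With all nulls true, a false claim requires the first step to be passed. Its chance is 1 − (1 − 0.0167)³ = 4.9% under independence, and at most 5% under any correlation. In a fixed sequence a false claim with all nulls true requires the lead test to be significant, so the error is at most 5%.

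**The case against.** The strongest reply is that this is only an omission. The SAP is not shown, the article refers to a full protocol held elsewhere, and alpha allocation is often settled in such documents. If silence were the whole point, that reply would succeed. It does not remove the conflict in the printed text: one section has a single primary outcome at the full 0.05, and the others have three. A rule in the SAP would still leave those sections to be reconciled, and a rule that split alpha would undercut the sizing at 0.05.

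Other parts of the reply stand and limit what may be said.

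- The article does not say that the 5% applies per test, or that one success suffices. The Objectives name knowledge and adherence together. If all outcomes had to succeed, there would be no inflation. Any-one-succeeds is a reading that the text leaves open, not one that it states.
- A reader might infer that the error is nearly three times 5% in all cases. That holds only near independence.
- A reader might cite knowledge, which an education session plus leaflets would most plausibly move, as an example of a false claim. If knowledge truly improves, the claim is true. The worry is then about what a positive trial means, not about type I error.
- A reader might infer that the trial was sized on GMAS. The Sample size section names no scale. GMAS is the natural reading, because the Background describes the cited trial as reducing non-adherence to medication, but it is not stated.
- Power for 16% against 9% with 619 × 0.8 / 2 ≈ 248 per arm is about 65% at 0.05 and 48% at 0.0167. These figures concern a binary outcome. The primary outcomes are changes in mean score, so the figures do not show what an adjustment would cost in this trial.

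**Conclusion.** The point holds as a conflict over which outcome is primary, together with a single 5% level applied to three primary outcomes without a rule. Under the assumptions listed above, the chance of at least one false primary claim is about 11% to 14% for correlations from 0 to about 0.7, roughly two to three times 5%. It is still 8.4% at 0.9.

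These are conditional figures and not the trial's established error rate. The article makes within-subject signed-rank tests its confirmatory analysis, so the error of a between-group claim could differ from any of them. That is a separate issue. The documents also do not support saying that the authors intend to claim success on any single outcome.

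**What to change.** Reconcile the Sample size section with the Abstract and Discussion by naming one lead primary outcome and its scale. Medication adherence on GMAS fits the cited basis best, but the sponsor must confirm it. Then state one of two rules:

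1. **Fixed sequence.** Test the lead outcome at two-sided 5%, then the other two in a stated order at the same level, stopping at the first non-significant result. The lead outcome loses no power. The cost is that later outcomes cannot be claimed if the lead outcome fails, even if their effects are real.
2. **Holm across the three.** No ranking is needed for the tests. The cost is some loss of power for each outcome, which cannot be quantified without standard deviations and expected differences on the score scales.

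Under either rule, report all three outcomes with 95% confidence intervals.

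The change itself is a matter of wording, but its timing is not trivial. Trial status says that the final results are being analysed, while the statistician is described as blinded to allocation. If the blind is intact, the rule should be written and dated before it is broken. If results by group have been seen, the rule should be disclosed as post hoc and adjusted p-values shown for all three outcomes.
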